## Abstract

**Background:**

Mobile health-based individualized interventions have shown potential effects in managing cardiovascular risk factors. This study aims to assess whether or not mHealth based individualized interventions delivered by an Individualized Cardiovascular Application system for Risk Elimination (*iCARE*) could reduce the incidence of major cardiovascular events in individuals with coronary heart disease.

**Methods:**

This study is a large-scale, multi-center, parallel-group, open-label, randomized controlled clinical trial. This study will be conducted from September 2019 to December 2025. A total of 2820 patients with coronary heart disease will be recruited from two clinical sites and equally randomized into three groups: the intervention group and two control groups. All participants will be informed of six-time points (at 1, 3, 6, 12, 24, and 36 months after discharge) for follow-up visits. Over a course of 36 months, patients who are randomized to the intervention arm will receive individualized interventions delivered by a fully functional *iCARE* that using various visualization methods such as comics, videos, pictures, text to provide individualized interventions in addition to standard care. Patients randomized to control group 1 will receive interventions delivered by a modified *iCARE* that only presented in text in addition to routine care. Control group 2 will only receive routine care. The primary outcome is the incidence of major cardiovascular events within 3 years of discharge. Main secondary outcomes include changes in health behaviors, medication adherence, and cardiovascular health score.

**Discussion:**

If the *iCARE* trial indeed demonstrates positive effects on patients with coronary heart disease, it will provide empirical evidence for supporting secondary preventive care in this population. Results will inform the design of future research focused on mHealth-based, theory-driven, intelligent, and individualized interventions for cardiovascular risk management.

**Trial registration:**

Trial registered 24th December 2016 with the Chinese Clinical Trial Registry (ChiCTR-INR-16010242). URL: http://www.chictr.org.cn/showproj.aspx?proj=17398.

**Supplementary Information:**

The online version contains supplementary material available at 10.1186/s12872-021-02153-9.

## Background

Cardiovascular disease (CVD) remains a leading cause of death worldwide including China, with about 50% of the deaths from coronary heart disease (CHD) [1, 2]. Each year, CHD causes an estimation of 7.3 million deaths globally, with a mortality rate of 115 per 10,000 reported from China [1, 2]. Individuals diagnosed with CHD are at high risk in developing major cardiovascular events (MACEs) following discharge [3], with incidences ranging from 6 to 25% [4, 5]. As shown in previous studies, the occurrence of MACEs for patients with CHD is associated with poor health outcomes, such as increased long-term mortality, reduced quality of life, increased health care costs and caregiver burden [6].

Identified cardiovascular risk factors for CHD and MACEs, such as unhealthy behaviors (including unhealthy diet, inadequate physical activity, smoking), elevated metabolic indicators (high cholesterol, high blood pressure, high blood sugar levels) and medication nonadherence, are highly modifiable [7]. According to the American Heart Association, promotion of ideal cardiovascular health should include the combination of ideal health behaviors and ideal metabolic indicators, which illustrates a greater impact on reducing incident MACEs than any single cardiovascular risk factor [8–10]. Addressing cardiovascular health in disease management was associated with a 68% and 45% reduction of incident MACEs and CHD mortality, respectively [5, 11, 12]. However, a low prevalence of ideal cardiovascular health was identified among patients with CHD, despite interventions in facilitating cardiovascular health have been developed and implemented [13–16]. Studies from Europe, the United States, and China showed that, about 40% to 80% of the patients with CHD were not adherent to health behaviors and medication treatment [12, 15–17].

Lack of individualized real-time feedback was identified as one of the main barriers preventing patients from adapting strategies for health behaviors and medication adherence [18]. A recent meta-analysis found that individualization was a possible approach for adults to effectively reduce weight, waist circumference, and blood pressure [19]. The concept of individualization is referred to the content of the intervention being created based on individuals’ existing behaviors, stages of behavior change, preferences, barriers, and other recognizable features [19]. However, despite individualized strategies were included in traditional interventions through one-on-one format, such approach was criticized as time consuming with extensive use of healthcare resources [14, 20, 21]. This greatly limited the implementational scalability of individualized interventions in promoting cardiovascular health [20, 21].

In overcoming the existing drawbacks of traditional interventions for facilitating adherence to health behaviors and medication, mobile health (mHealth) based interventions were brought into play, which allowed cost-effective delivery of individualized interventions and real-time feedback [22, 23]. However, inconsistent findings and suboptimal effect on facilitating adherence to health behavior and medication have been reported [24–26], with evidence on the MACEs reduction remained unconvincing [24–26].

Several barriers may have prevented the effect of mHealth interventions from achieving their optimal results. Firstly, the interventions delivered by existing mobile tools were mostly simple, and they were not actually reflecting individualized contents with real-time feedback [27, 28]. Secondly, the effect of individualized mHealth-based interventions for facilitating adherence has not been well established in large-scale and long-term randomized control trials [29, 30]. Thirdly, only limited number of mHealth based interventions addressed multiple CHD related risk factors, with about 80% only focused on one of the health behaviors, such as diet and smoking [24, 31]. Fourthly, a theory-driven approach was often lacking in designing the mHealth interventions [28, 32], with limited emphasis on evidence-based content [33]. Lastly, text-messaging was the most commonly used method for delivering mHealth-based interventions [29]. It was criticized that text-messaging might be unattractive to engage patients in the interventional activities over a longer period [34]. Interestingly, application of visual contents such as videos, comics, and pictures are better fitted for meeting patients’ preferences, therefore can possibly improve the attractiveness of mHealth interventions [35]. A recent study on visualization of asymptomatic atherosclerotic disease for optimum cardiovascular prevention provides evidence to support the contributory role of pictorial presentation on CVD prevention [36]. However, whether or not mHealth interventions delivered via visual modes can effectively promote health behavior change and medication adherence in CHD patients, therefore leading to a reduced incidence of MACEs, is unclear [36].

### Preliminary work: iCARE system

In order to facilitate ideal cardiovascular health therefore reducing the incidence of MACEs in patients with CHD, we developed an **I**ndividualized **C**ardiovascular **A**pplication system for **R**isk **E**limination (*iCARE*). The development process and the functions of the *iCARE* system were described in our preliminary work (Additional file 1). In summary, the *iCARE* system was developed based on a user-centered approach as suggested by previous research [37]. We incorporated a set of IF–THEN algorithm triggering interventions to ensure patients receiving individualized recommendations and real-time feedbacks for facilitating adherence to health behaviors and medications. The interventions of the *iCARE* were developed based on the intervention mapping framework and the Contemplation-Action-Maintenance (CAM) behavior change model for CHD patients [38]. The needs and preferences of patients with CHD, as well as professional opinions of nurses and clinicians who are specialized in CHD were fully considered during the development process. The *iCARE* system includes a patient app, a care-provider app for healthcare professionals, and a cloud platform. The main functional components of the *iCARE* system are displayed in Additional file 1.

This study protocol is aimed to describe the implementational plan for a randomized controlled clinical trial in which the effect of the individualized, visualized, comprehensive interventions delivered by *iCARE* on MACEs reduction for patients with CHD will be evaluated. Meanwhile, the study plan for testing the effects of the *iCARE* on facilitating adherence to recommended health behaviors (including healthy diet, regular physical activity, and smoking cessation) and medications will also be described.

## Methods

### Study design

The *iCARE* study is a multicenter, open-labeled randomized controlled trial with three parallel groups conducted among patients with CHD. The *iCARE* trial has been registered at Chinese Clinical Trial Registry in December 2016 (ChiCTR-INR-16010242) prior to participants’ recruitment. This trial will be conducted in accordance with the SPIRIT 2013 statement [39] and the Consolidated Standards of Reporting Trials (CONSORT) for Web-based and Mobile Health Interventions [40]. The results will be reported according to the CONSORT guidelines [41]. This study is approved by the Institutional Review Committee of the Capital Medical University (Approval No. 2015SY45) and the study hospitals (Beijing An-Zhen Hospital, Approval No. 2015030; Beijing Chao-Yang Hospital, Approval No. 20211224). Written informed consent will be obtained from all patients who meet the inclusion criteria and are willing to participate before randomization.

### Settings and participants

Eligible patients will be recruited from three cardiac wards and one emergency ward in two university affiliated hospitals. All participants will be followed up for a total of three years (with six time-points for data collection). Patients will be included in the study if they: (a) are 18 years or older; (b) have a documented diagnosis of CHD including acute myocardial infarction (AMI), acute coronary syndrome (ACS), or undertake a percutaneous coronary intervention (PCI) either as emergency or elective procedures; (c) have at least one smartphone with Android system and use it daily, and (d) agree to participate. We choose smart phones with android system to install the *iCARE* as they are more popular and affordable in China [31].

The exclusion criteria include: patients who are (1) with a history of psychiatric and neurological disorders; (2) unable to speak or understand Mandarin; (3) illiterate; (4) with impaired bilateral hearing, or visual impairment which limits the use of smartphone; (5) with contraindications or severe physical disabilities that limit patients from participation; (6) with severe medical conditions; and (7) participating in other ongoing clinical trials or prospective cohort studies. Additional exclusion criteria will be applied if patients are not able to understand the procedure and the aims of the study after full explanation, or not able to fill in the questionnaires during the baseline visits.

### Recruitment, screening, and baseline visits

To identify eligible patients, a targeted review of patients’ medical record based on the inclusion and exclusive criteria will be carried out, with referrals from nurses or clinicians within the study sites. Identified patients with CHD will participate in a formal screening session and have a baseline visit in the hospital. During the formal screening session, we will ask patients to complete an initial screening assessment which includes age, educational background, vision, hearing, diagnosis, heart function grade, etc. Patients who meet the study criteria will be asked to sign a written informed consent before attending the baseline visit. Participants’ baseline data will be collected via the *iCARE* care-provider app and patient app within one week of enrollment, which includes patients’ general characteristics, health behaviors (daily diet, physical activities, smoking status) and medication adherence in the past 30 days before admission, as well as their blood pressure, blood glucose, blood lipid levels during hospitalization.

### Randomization and blinding

In this proposed study, three versions of *iCARE* apps will be installed on participant’s smart phone based on their group assignment (Additional file 1). Study investigators will assist participants in each group to download, register and log into the designated *iCARE* app:*iCARE*-1: is fully functional with individualized interventions delivered via multiple visual displays such as comics, videos, pictures, and text to address all the factors in the CAM model plus routine care;*iCARE*-2: is fully functional but all interventions are delivered only via text which did not address all factors in the CAM model plus routine care;*iCARE*-3: has limited function which only allows patients for daily data entry.

After baseline data collection, participants will be randomized to one of the three groups: the intervention group (*iCARE*-1 plus routine care), the control group 1 (*iCARE*-2 plus routine care), or the control group 2 (*iCARE*-3 plus routine care), following stratified block randomization. The randomization will be computer-generated by a statistician who will not have any active involvement in the study. The block size will be set at 15 with the allocation ratio set at 1:1:1 to ensure balance among three study groups. Participants will be stratified by 4 wards and their smoking status. The randomization assignment will be generated randomly, numbered consecutively, and will be kept in a sealed, opaque envelope. Patient assignment will be revealed to study researchers only after participants completed their baseline visit. This proposed study is an open-labeled trial as participants are fully aware of their intervention allocation, and the group assignments were known to study investigators. However, researchers who perform data analysis, and clinical staff who conduct laboratory testing will be unaware of the group assignment.

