### Study status and recruitment

The participant recruitment process has started since September 2019 and is in progress. As recruitment is planned to be finalized in December 2022 and patients will be followed for 3 year, the final study results will be first available by December, 2025. Therefore, data cleaning or analyses are not yet started at the time of submission.

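### A single published block size of 15, in an open-label trial still recruiting, leaves up to 9.1% of assignments deducible: a modest and avoidable risk of selection bias

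*Protocol article*

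**What the plan says.** All but the last of these points come from the protocol article, Randomization and blinding.

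- **Method:** allocation is made "following stratified block randomization", and "The block size will be set at 15 with the allocation ratio set at 1:1:1 to ensure balance among three study groups". No other size is mentioned, and nothing says that the size is kept from recruiting staff.
- **Strata:** "Participants will be stratified by 4 wards and their smoking status". The number of smoking levels is not given. Two levels make 8 strata, three make 12.
- **Who knows past assignments:** the trial is open-label and "the group assignments were known to study investigators". The same section adds: "Study investigators will assist participants in each group to download, register and log into the designated" app, and each arm has its own version.
- **Safeguards:** a statistician with no active part in the study generates the sequence by computer. Assignments are "numbered consecutively, and will be kept in a sealed, opaque envelope", and an assignment is revealed only once the baseline visit is complete.
- **Timing:** Study status and recruitment reports that "The participant recruitment process has started since September 2019 and is in progress", with completion planned for December 2022.

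**The concern.** Sealed envelopes and late reveal stop anyone from reading the next assignment. They do not stop anyone from working it out. If every block holds exactly five of each arm and earlier assignments are open, a tally by ward and smoking status shows which arms are used up as a block closes. The article makes the length, ratio and strata public during enrolment.

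There is some room to act on such knowledge. Under Recruitment, screening, and baseline visits, patients come by record review and by referral from ward nurses and clinicians. Under Settings and participants, some exclusions call for judgement: severe medical conditions, failure to understand the study, and inability to complete the baseline questionnaires. The last can be applied until just before allocation. These features plausibly relate to event risk and to use of the app, and an intention-to-treat analysis cannot undo selection that took place before randomisation.

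The planned effect is 10% against 6% in 752 patients per group, that is 75.2 against 45.1 events, a difference of about 30. With a signal of that size, a cheaply avoidable source of bias is worth removing.

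**Working it through.** **Inputs.** Block size 15, three arms at 1:1:1, so k = 5 per arm; strata as above; total 2820 (Sample size calculation and power analysis); recruitment September 2019 to December 2022 (Study status and recruitment).

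**The plan's own figure.** The article derives nothing from the block size; its only derived figure is the sample size. The Schoenfeld formula with hazard ratio 0.6, two-sided alpha 0.05 and 80% power gives 120.3 events, and 120.3 / (0.10 + 0.06) = 752 per group. Then 752 / 0.8 = 940, and 3 × 940 = 2820. The figure reproduces and is not affected by this point. 2820 / 15 = 188 blocks if all are complete.

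**1. Assignments known with certainty.** An assignment is certain when both other arms are used up, meaning that it comes after all 2k = 10 assignments to those arms. The chance is 1/(2k + 1) = 1/11 = 9.1%. Per block this is 15 × 1/11 = 1.36. Over 188 blocks it would be 256.

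For comparison, the same formula gives 1/5 = 20.0% for blocks of 6 and 1/3 = 33.3% for blocks of 3.

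**2. Intervention yes/no already known.**
- The intervention is used up: each of the 10 control assignments falls after all five intervention assignments with chance 1/6, so 10/6 = 1.667.
- Only the intervention is left: each of the 5 intervention assignments falls after all ten others with chance 1/11, so 5/11 = 0.455.
- Sum: 2.12 per block, and 2.12 / 15 = 14.1%.

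**3. Best guess.** Always naming the arm with most places left is right in 7.46 of 15 assignments by exact enumeration, that is 49.7% against 33.3% by chance.

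**4. Effect of a queue.** Steps 1 to 3 take every earlier assignment in the stratum as seen. The chances that the last 1, 2, 3, 4 or 5 assignments of a block are all to one arm are 1, 4/14 = 0.286, 0.066, 0.011 and 0.001, which sum to 1.364.
- One patient ahead and not yet allocated: the first term drops out, leaving 0.364 per block (0.364 / 15 = 2.4%).
- Two ahead: 0.078 per block (0.5%).

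Assuming even accrual, 2820 patients over 40 months (about 174 weeks) is about 16 a week, or about 2 per stratum per week with 8 equal strata and about 1.4 with 12. Baseline data may be collected up to a week after enrolment, so one or two pending patients are plausible. The range is then 0.5% to 9.1%.

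**5. Varying the block size.** This was simulated over 3000 blocks per set. The observer is assumed to know the set of sizes and to tally every assignment, but not to be told where blocks end.

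| Block sizes | Certain | Intervention yes/no known | Best guess right |
|---|---|---|---|
| Fixed 15 (exact) | 9.1% | 14.1% | 49.7% |
| 12, 15, 18 | 1.6% | 2.6% | 49.6% |
| 9, 12, 15 | 2.0% | 3.1% | 51.1% |
| 6, 9, 12, 15 | 1.5% | 2.6% | 51.8% |

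Simulating the fixed size as a check gave 9.0%, 14.0% and 49.9%.

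**The case against.** **Those who recruit may not see assignments.** The article says that study investigators know the assignments and help install the apps, and that ward staff refer patients. It does not say that these are the same people. This stands. A reader might infer that recruiters foresee allocations and that concealment has failed, but the article supports only the possibility.

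**9.1% is a ceiling.** It needs a complete tally and nobody waiting in the stratum. Consent comes before baseline and allocation after it, so places are filled in the order in which baselines finish. Smoking status is itself listed among the baseline data, so the stratum may have to be read from the chart when a patient is approached. This stands for decisions at approach. It has less force for an exclusion at the end of the baseline visit, when the stratum is known and the queue may have cleared.

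**The whole-trial count overstates what can be changed.** A reader might take 256 of 2820 as the number of patients at stake. It includes everyone enrolled since September 2019. A change reaches only later patients, whose number is not given, and publication could inform guesses only from then on.

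**The remedy is partial.** A reader might expect varied blocks to make the sequence unpredictable. They remove most of the certainty but leave the best-guess rate near 50%. This stands.

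**The design already has sound safeguards, and 15 is a large block for three arms.** This also stands, and it is why the risk is modest. Neither feature prevents deduction from a tally.

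**Conclusion.** The point holds as a modest, avoidable risk of selection bias. The article fixes and publishes one block size in an open-label trial that is still recruiting. For someone who sees every earlier assignment in a stratum, knows the size and has no pending patients to allow for, 9.1% of assignments are certain, and intervention yes/no is known for 14.1%. With one or two patients waiting, the certain share is about 2.4% or 0.5%.

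The article contains no wrong figure or contradiction here, and no evidence that anyone predicted an assignment. The sample size is unaffected. The case for a change is that it is standard and cheap and removes most of the certain predictions.

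**What to change.** For the remaining enrolments, the independent statistician issues new lists in the same strata, still "with the allocation ratio set at 1:1:1", with block sizes varying at random. A set such as 12, 15 and 18 avoids small blocks and does not raise the best-guess rate. The sizes are withheld from recruiting staff and not published until recruitment ends.

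Replace the fixed-15 sentence with, for example: *Blocks of randomly varying size will be used within each stratum; the sizes are held by the independent statistician and will be reported after recruitment closes.*

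For every 100 patients still to be enrolled, the most that could be certain falls from about 9.1 to about 1.6, and those with known intervention status from about 14.1 to about 2.6.

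Costs:
- One new set of lists and envelopes.
- At most one incomplete block per stratum at the changeover, so 8 or 12 in all. In each, two arms can differ by at most five patients.
- An amendment. The Intervention group section says that the design will stay as described once recruitment starts. The amendment should note this one exception and state that arms, ratio, strata, outcomes and analysis are unchanged.
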